### Control group

The children in the control group will not receive a ‘S&G exercise intervention package’ but will receive and wear wearable devices-Actigraph wGT3X-BT (Pensa- cola, FL) accelerometers. Research assistants will send helpful nutritional and exercise tips via WeChat message.

### Intervention

We used WeChat as the social media platform to carry out the intervention. A WeChat group is created for each group by the investigators. The intervention group will receive skipping rope plus the ‘gamification exercise package’. Data will be collected five times: at baseline, at end of intervention period, in the follow-up time at months 3,6,12.

### Nominated helpers-parents

Children can nominate their parents to be an official helper. The official helper will represent children and report daily information to the WeChat group. Children lack willpower and this way also may have potential benefits for children via increased support and motivation.

### Exercise protocol

There is strong scientific evidence that exercise substantially have well-documented health benefits including reducing metabolic disease risk and body fatness [12]. To achieve these benefits, WHO recommends that the level of exercise for a 5–17-year old is 60 min per day at moderate-to-vigorous intensity level.

The skipping rope was chosen as the main form of exercise intervention because it adopts the high popularity and acceptance among Chinese primary school students, as it was set to be tested by The State Education Bureau of China. Moreover, the skipping rope meet the WHO exercise recommendation for children and benefit for child growth. Additionally, considering the condition that pupil in shanghai primary school have physical education class which lasts 45 min every day, so we decide to set the volume of exercise as rope skipping for 1000 (approximately 10–15 min) per day.

Previous review indicate that no less than 6 months of intervention was the most effective duration, so the project is consisting of a 6-month intervention period and a 12-month follow-up period.

### ‘S&G exercise intervention package’

The intervention lasts for six months. It will be delivered via a smartphone app (WeChat) and an Actigraph wGT3X-BT. Several behavioral change theories will guide the intervention, including Social Incentive Theory and Gamification Theory.

### Social incentive intervention design

Previous research has found that a combination of individuals and teams could increase participants’ engagement [33]. Peer support, accountability and team discussion also has been proved to enhance social incentives [34]. Thus the intervention will add these features to promote enduring involvement:Grouping: In order to enhance social incentives, WeChat groups are established respectively for the intervention group and the control group by the investigators. The intervention group will be divided into 30 teams involving 6–7 members according to BMI, age and sex. Because a pilot study has showed that one group within 5–6 members had the best partner interaction [35].A kick-off meeting: After randomization, a kick-off meeting will be organized by the investigators and all participants in the intervention group will be asked to attend. In the meeting, the investigators will introduce the intervention protocol and ensure teammates fully understand what they need to do. Then, each team will perform several interactions to foster familiarity and cohesion among their teammates, as well as elect their team leader. A kick-off meeting can increase effective and positive interaction in social groups and promote engagement as well as motivation [36].Daily Report within Teams: Parents urge the children to skip rope every day and report the daily information (include: data recorded by Actigraph wGT3X-BT; ‘whether the number of rope skipping reach the standard’) to their team WeChat group before 22:30 PM on the day.Peer Support: Each day teammates (the family who represent child) develop at least one interaction in the WeChat group. Praising teammates who reach the standard and encourage those who don’t reach (e.g., ‘Doing well and keep going.’) are also required. Criticism and ridicule, which might cause negative reactions, are not allowed.Accountability: Team leader responsibility system is implemented in the group. The team leader is responsible for reminding their members to complete daily task and send “PS” (the abbreviation of peer support). The team leader rotates once every month for fairness.Team discussion: Healthy tips will be posted by the study team in each group every Friday. Participants will be guided to read it and communicate with teammate on their gains as well as barriers of the program.

### Gamification intervention design

Points, ranking, badges, punishment and reward are typical elements of gamification, and have been confirmed as effective techniques to improve the interest, incentive and purposiveness of non-game programs [27, 37]. They will be used within the intervention, and to encourage frequent use and support ongoing engagement of both participants and helpers. The detail elements are as follows:Points: Each week, the members and teams will be rewarded for the successful accomplishment of specified activities. The activity consists of four parts, including peer support, daily report, the weekend competition and tip reading. Different types of activities will result in different pinots. For example, if an individual reports daily information on time, he or she would earn 5 points per day; reading tips earn 5 points per day. If they take part in the competition on weekend, earn 20 points. The points leaderboard see Fig. 2.Ranking: Each week, every member in a team and all teams will be ranked according to the final points, and ranking will be announced every Sunday.Badges: Different points set different badges. It is suitable for both teams and individuals. All will begin in the bronze level. Higher levels include silver, gold, and platinum. The example sees Fig. 3. The higher the point, the higher the level. In addition, the advanced individuals award the certificates to motivate and encourage all participants to compete with one another.Punishment: If a member does not finish daily task (or forget to do), the person will be asked to do some performances in WeChat group such as posting a voice messages of song, a standup comedy, or a dance video. Besides, if team leader fails to urge teammate on time, the leader also need to perform. Utilizing performance as punishment is an original design and it could not only urge participants to follow the rules yet avoid embarrassment, but also improving compliance.Rewards: Once a month, each member of the team that accumulated the highest points will be rewarded with a diploma. Besides, the team which get high point will be rewarded corresponding badges as their WeChat group name and it will be showed in a leaderboard.Competition: Every weekend, each team will hold a skipping competition online (or offline for their convenient) in order to stimulate the teammates to engage in teamwork. The content is the number of rope skipping in one minute. All members will participate in the competition in principle, and the one who does best or the team which get the highest score at rope skipping will be rewarded with a virtual certificate, respectively. In addition, each team will calculate the per capita number for ranking.

**Fig. 2 Fig2:**
[figure not shown]
Template for the points leaderboard. Ranking was determined by total points. All participants could access the leaderboard to see their ranking and badges in comparison with all others

**Fig. 3 Fig3:**
[figure not shown]
The example of the badges

### Message and feedback

Participants have regular contact with the study team each week via WeChat message to ascertain if there are any difficulties such as changing exercise habits and how they are uploading the information. These messages are structured and standardized, and all participants in the intervention group receive the same message. The contents of these messages are composed using motivational language and feedback is encouraged which is recorded to help assess compliance with the intervention.

### Outcome measures and measurement procedures

A full list of measurable outcomes is presented in Table 1. Participants will be assessed at baseline, at end of intervention period, in the follow-up time at months 3,6,12. Assessment will be undertaken by an experienced research health workers from primary school and Shanghai children’s hospital. All staff involved in data collection will be given training in study procedures before the study.

**Table 1 Tab1:** Summary of outcome measures

Outcome	Item	Device
*Primary outcomes*		
Metabolic indices	Fasting glucose, triglyceride, total cholesterol, HDL-C, LDL-C, insulin, HbA1c and blood pressure	Blood analyze and blood pressure measurement
*Secondary outcomes*		
Healthy behavior	Diary PA	Accelerometer (Actigraph wGT3X-BT; 7 consecutive days, 24 h/day); IPAQ-A questionnaire
	Diet	DSQ (Dietary Screener Questionnaire)
	Sleep health	Accelerometer (Actigraph wGT3X-BT; 7 consecutive days, 24 h/day); PSQI questionnaire
	Screen media use	Self-designed questionnaire
Anthropometric	BMI, height, weight, waist circumference, body fat rate and muscle mass	Physical examination

*DSQ* Dietary Screener Questionnaire, *PSQI* The Pittsburgh Sleep Quality Index, *IPAQ-A* International Physical Activity Questionnaire

Biomarkers: We will use a basic panel of tests to evaluate a comprehensive metabolic profile using overnight fasting blood draw. After an overnight fast of at least 10 h, 5 ml venous blood samples will be taken from the antecubital vein and collected for measuring biochemical parameters [38]. All biochemical analyses on blood will be carried out at a validated biomedical analyses laboratory. Fasting glucose, triglyceride, total cholesterol, HDL-C, and LDL-C were analyzed. Insulin resistance will be estimated using the homeostasis model assessment of insulin resistance (HOMA-IR) = (fasting insulin (FI) x fasting glucose (FG)/22.5, and insulin β cell base secretion index (HOMA-β) = 20 *FI/(FG-3.5) [39].Anthropometric measures: We will measure height, weight, waist circumference and muscle mass via Tanita BC-420 body composition analyzer. BMI (kg/m^2^) is the standard diagnostic tool to assess obesity and overweight in the children and will be calculated as body weight (kg) divided by the square of height (m). Height will be measured using a Seca Leicester Height Measuring Stadiometer, with participant facing forward, wearing no shoes and with their head in the Frankfort Plane (parallel to the floor). Measurements will be recorded once, in cm, to one decimal point. Weight will be measured, in the absence of shoes, using Tanita HD 352 High-Capacity Low-Profile Electronic Weighing Scales. Scales will be calibrated before first use. Weight will be recorded once, in kg, to one decimal point. Waist circumference will be measured using a 2 m flexible tape measure with buckle, around the midpoint between the iliac crest and inferior margin of the lower rib. Muscle mass will also be measured. Blood pressure will be measured at least 2/3rd of upper arm using appropriate sized cuff encircling, and at two times: initially after sitting quietly for 10 min, then again after 2 min using Mercury sphygmomanometer (model XJ1ID, China).Health behavioral outcome measurements: The daily PA, screen media use, dietary behaviors and sleep health will be assessed.

The daily PA assessment including direct measures and indirect measures. For direct measures, daily PA will be measured using Actigraph wGT3X-BT accelerometers, which can provide objective as well as accurate measurement, and a valid and reliable estimate of PA in young people [15, 40]. Children will be instructed to wear the accelerometer on the non-dominant wrist for 7 days during waking hours (except during water-based activities) [41, 42] to measure duration, intensity and frequency of activity. To collected data of types of daily PA, self-administered Short form of International Physical Activity Questionnaire (IPAQ-A) will be used to subjectively measure daily PA. IPAQ-A is designed for large-scale research surveillance of adolescent PA [43]. Main questions in IPAQ-A assess PA habits by frequency; includes questions specific to school-related PA: during physical education, recess, at lunchtime, right after school, and evening and past weekend physical activities.

Additionally, questionnaires were designed to collect data about time of screen media use and dietary behaviors. Parents, guided by the study team, will report the number of minutes per day of screen media use (e.g., television, mobile electronic devices, video games and computers). Diet will be measured by a validated Dietary Screener Questionnaire (DSQ), a 26-item questionnaire which asks about the frequency of consumption in the past month of selected foods and drinks for children [44].

Assessment of sleep health will include both objective sleep parameters (total sleep time, sleep onset latency, sleep efficiency, and wake after sleep onset) and subjective parameters (sleep quality). Objective sleep parameters will be assessed using an accelerometer (Actigraph wGT3X-BT) for 7 consecutive days, 24 h/day. The Pittsburgh Sleep Quality Index (PSQI) was used to assess the subjective sleep quality and disturbances over a month time interval. It contains 18 items, generating seven scores, through the sum of score to assess the sleep quality. The higher the score, the worse the sleep quality [45].

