**Methods:**

We propose a randomized controlled trial of a ‘S&G exercise intervention’ among 420 overweight and obese children who have at least one marker of metabolic syndrome. Children will be randomized to control or intervention group in a 1:1 ratio. The exercise intervention package includes intervention designs based on integrated social incentives and gamification theory, involving targeted essential volume and intensity of activity (skipping rope) as well as monitoring daily information and providing health advice by WeChat. Participants will undertake assessments at baseline, at end of intervention period, in the follow-up time at months 3,6,12. The primary outcome is outcome of metabolic health. Secondary outcomes include behavioral (e.g., diary physical activity, diet) and anthropometric measures (e.g., body fat rate and muscle mass).

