### Sample size consideration

Based on the relative studies on exercise intervention with obese children [29], the sample size required for each group was estimated to be about 175 with a power of 80%, an α of 0.05, and assumed an effect size of 0.30. Therefore, a total of 350 children are need. To account for 20% loss-to-follow-up, a total of 420 children will be recruited.

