### Statistical analyses

Descriptive statistics will be calculated using mean (SD) for continuous variables and n (%) for categorical variables. Differences will be compared using independent t-tests for continuous variables (e.g., blood sample outcomes) and Chi-squared tests for categorial variables (e.g., education and household income of parents). Linear mixed models will be used to test for group differences on the main outcome variables at follow-up visits, while subject ID will be random effect, the main effect include time, treatment group, and the interaction between time and treatment. We will include covariates that are not balanced between two groups into the model. Data will be entered and cleaned with EpiData 3.0, and managed and analyzed using SPSS 24.0 and SAS. Statistical significance will be set at *P* < 0.05.

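### All eight metabolic indices are primary at an unadjusted 0.05, with no lead index, primary visit or success rule, while the sample size covers one unnamed comparison

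*Protocol article*

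**What the plan says.** The Abstract names a domain and no variable: "The primary outcome is outcome of metabolic health". Table 1, in Outcome measures and measurement procedures, expands that domain under a plural primary heading into "Fasting glucose, triglyceride, total cholesterol, HDL-C, LDL-C, insulin, HbA1c and blood pressure". That is eight items. The Inclusion criteria give systolic and diastolic pressure separate cut-offs, so blood pressure is two variables and the count becomes nine. HOMA-IR and HOMA-β are defined in the same section but appear in neither tier of Table 1.

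On timing, the Intervention section says: "Data will be collected five times: at baseline, at end of intervention period, in the follow-up time at months 3,6,12". That makes four post-baseline assessments.

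On analysis, the Statistical analyses section says: "Linear mixed models will be used to test for group differences on the main outcome variables at follow-up visits". The model terms are given as "the main effect include time, treatment group, and the interaction between time and treatment". The section closes with one general rule ("Statistical significance will be set at" P < 0.05). It mentions no ordering of outcomes, no adjustment and no number of indices that must succeed.

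Sample size consideration gives a per-group size of "about 175 with a power of 80%, an α of 0.05, and assumed an effect size of 0.30", then 350 in total and 420 after an allowance for 20% loss. The effect size is tied to no index and no visit.

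**The concern.** The trial's main conclusion is whether the package improves metabolic health. As written, nine variables can each support that conclusion at the full 0.05, at visits that are not ranked. Nothing says whether one significant index is enough, whether several are needed, or which visit decides. The timing text also lists the end of intervention apart from the follow-up months, so it is not clear that the end of intervention is among the follow-up visits tested.

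Two things are at stake. The error rate behind a positive claim is not the 0.05 that the plan states. And the stated 80% power belongs to a single test that the plan does not identify, so it cannot be attached to any result the trial will report.

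**Working it through.** **Inputs from the protocol article.** Eight primary items, nine variables with blood pressure split (Table 1, Inclusion criteria). Four post-baseline assessments (Intervention). Threshold 0.05, taken as two-sided because the text does not say (Statistical analyses). Effect size 0.30, alpha 0.05, power 80%, 175 per group, 420 recruited, 20% loss (Sample size consideration). The documents give no correlations between indices or visits, so these are assumptions and are shown as ranges.

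**1. The plan's own figure.** n per group = 2 × (1.960 + 0.842)² / 0.30² = 174.4, rounded up to 175. The stated 175 is reproduced, and it is the size for exactly one two-sided test at 0.05.

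**2. One test per variable, no true effect on any.** If the tests are independent, the chance of at least one significant result is 1 − 0.95^k:
- k = 8: 1 − 0.95^8 = 33.7%
- k = 9: 1 − 0.95^9 = 37.0%

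For correlated tests I simulated equicorrelated normal statistics (200,000 draws). Each cell gives any false positive, then false benefit only:

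| Common correlation | 8 indices | 9 variables |
|---|---|---|
| 0 | 34% / 18% | 37% / 20% |
| 0.2 | 32% / 16% | 35% / 18% |
| 0.3 | 30% / 15% | 33% / 16% |
| 0.5 | 25% / 13% | 27% / 13% |

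The false-benefit column counts one tail only. Its independent value is 1 − 0.975^9 = 20.4% for nine, against 2.5% for one test. An uneven pattern (total cholesterol with LDL-C 0.85, systolic with diastolic 0.65, the rest low to moderate) gives 33% for nine variables.

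**3. The same nine variables tested separately at four visits (36 tests).** With between-index correlation 0.2 to 0.5 and between-visit correlation 0.6 to 0.7, the chance of any false positive runs from about 57% (0.5 and 0.7) to about 73% (0.2 and 0.6). False benefit alone is about 30–42%. A wider grid (0.1 to 0.7 between indices, 0.5 to 0.9 between visits) gives 34–78% for any false positive.

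**4. Power at effect size 0.30 (two-sample t test).** A 20% loss from 420 leaves 420 × 0.8 = 336, or 168 per arm.

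| | 175 per arm | 168 per arm |
|---|---|---|
| One variable, alpha 0.05 | 80% | 78% |
| Each of nine, alpha 0.05/9 = 0.0056 | 51% | 48% |

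By the normal approximation at 175 per arm, the expected z is 0.30 × √(175/2) = 2.81. The critical value is 1.96 for one test and 2.77 for alpha 0.05/9, which is why power falls to about one half. Regaining 80% per index under an equal split would take 291 per arm before loss.

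**The case against.** The strongest reply is that this is a condensed article and that a multiplicity method and key contrast commonly sit in a statistical analysis plan, which is not shown. That is fair for the method. It does not reach what the article itself fixes: every index primary, one 0.05 threshold, and a sample size for one unnamed comparison. A later plan that picked one index or visit would be changing the published primary outcome.

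A second reply is that the Statistical analyses section never says each visit is tested separately. One time-by-treatment test per variable fits the wording equally well. This stands. The 57–73% figures belong only to the visit-by-visit reading, and the one-test reading is the base case.

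Third, a reader might infer that an ineffective package would more often than not produce a positive trial. The documents do not support that. With one test per variable the chance is about one in four to just over one in three. About half of those false positives would point to harm, and false benefit stays below one half even with four visits under the assumed correlations. The plan also contains no rule that any single index is enough. That reading has to be supplied, and the fair statement is that the success criterion is undefined.

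Fourth, a reader might argue that admitting children with any one abnormal marker makes a 0.30 SD shift on every index unattainable. The outcomes are continuous, no baseline distribution is given, and total cholesterol, LDL-C and insulin are not eligibility markers at all. The documents give no basis for that step.

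**Conclusion.** The point holds. The protocol declares nine variables primary at an unadjusted 0.05 and fixes neither the index, the visit nor the rule by which the trial succeeds. Its power statement covers only one of the possible tests, and that test is not named.

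The size of the error depends on two things that the article leaves open. If any significant index counts as success and each variable is tested once, the two-sided family-wise error is about 25–37%, five to seven times the nominal 5%. It drops below 30% only when the common correlation reaches roughly 0.3 (eight indices) or 0.4 (nine variables). If visits are also tested separately, it is about 57–73%. The correlations are assumptions, and so is two-sided testing. The counts of variables and visits, the threshold and the single-comparison sample size are read directly from the text.

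This should be settled before results are seen, because it governs the trial's main claim.

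**What to change.** 1. Name the end of the 6-month intervention as the primary visit, and say explicitly that it is the contrast taken from the mixed model.
2. Choose one of two options:
   - one primary variable at that visit, either a single index or a pre-specified composite; a composite needs its own effect-size justification, because nothing in the article shows that 0.30 applies to it;
   - all nine variables primary at that visit, with Holm or Hochberg across them. Holm needs no assumption about their correlations, whereas Hochberg does.
3. Make HOMA-IR, HOMA-β and the later visits secondary, and also the remaining indices if one variable is named. Align the Abstract and Table 1.
4. Restate the power for the chosen option. For a single variable with effect size 0.30, state 80% with 175 per arm and about 78% with the 168 expected after loss. For nine variables, state at least 51% and 48% per index. These are the equal-split values, and Holm and Hochberg are no less powerful than that split.

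The change is to wording in the Abstract, Table 1, Sample size consideration and Statistical analyses. No new data are needed. The price is that single-index and later-visit results become secondary evidence, or, if all nine stay primary, that power per index falls.

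### Accelerometer wear is waking hours only in the activity text but 24 h/day in Table 1 and the sleep text; if the waking-hours instruction is the one given, the objective sleep outcomes cannot be derived

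*Protocol article*

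**What the plan says.** All the wear statements are in the protocol article under Outcome measures and measurement procedures.

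- **Activity paragraph.** The device is named: "daily PA will be measured using Actigraph wGT3X-BT accelerometers". Children are to be instructed to "wear the accelerometer on the non-dominant wrist for 7 days during waking hours", with an exception for activities in water. The stated purpose is to capture how long, how hard and how often the child is active.
- **Table 1, daily physical activity row.** "Accelerometer (Actigraph wGT3X-BT; 7 consecutive days, 24 h/day); IPAQ-A questionnaire".
- **Table 1, sleep health row.** "Accelerometer (Actigraph wGT3X-BT; 7 consecutive days, 24 h/day); PSQI questionnaire".
- **Sleep paragraph.** The planned measures are "objective sleep parameters (total sleep time, sleep onset latency, sleep efficiency, and wake after sleep onset", together with subjective sleep quality. On wear: "Objective sleep parameters will be assessed using an accelerometer (Actigraph wGT3X-BT) for 7 consecutive days, 24 h/day".

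Activity and sleep health are both secondary outcomes in Table 1. Both are also named in the second study aim at the end of the Background section.

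**The concern.** One device model has two wear rules, and for physical activity the two rules apply to the same outcome. The waking-hours rule is the one worded as an instruction to the child, so it is the one most likely to be carried into a participant leaflet or a staff briefing.

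Two things are at stake. First, the objective sleep measures depend on recording through the night, and nights that were not recorded at baseline cannot be recovered later. Second, if some families remove the device at bedtime and others do not, the length of the record differs between children for reasons unrelated to their behaviour. Accelerometer summaries are then not comparable from child to child.

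**Working it through.** No sample size, power or error-rate figure is involved, so there is no plan figure to reproduce. The check sets the statements side by side.

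| Place | Outcome | Days | Daily wear |
|---|---|---|---|
| Activity paragraph | Physical activity | 7 | Waking hours, not in water |
| Table 1, activity row | Physical activity | 7 consecutive | 24 h |
| Table 1, sleep row | Sleep | 7 consecutive | 24 h |
| Sleep paragraph | Sleep | 7 consecutive | 24 h |

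**Step 1: is the conflict real?** Rows 1 and 2 concern the same outcome and the same device model and give different daily wear. No reading satisfies both.

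**Step 2: would separate recording periods remove it?** The article does not say whether activity and sleep are recorded in the same week. Suppose there were one waking-hours week for activity and one 24 h week for sleep. Rows 1, 3 and 4 would then be compatible, but row 2 would still contradict row 1. The article also describes no separate sleep week and no separate night-wear instruction.

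**Step 3: what is lost under waking-hours wear?** Sleep onset latency needs the record from going to bed until falling asleep. Total sleep time, sleep efficiency and wake after sleep onset need the record from falling asleep until the final waking. A device taken off for the night records none of this, so 4 of the 4 objective sleep parameters are lost. The article schedules five assessments (baseline, end of intervention, and follow-up months 3, 6 and 12), and the loss recurs at each one where that instruction is used.

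As an illustration only, assume a child sleeps 8 to 10 h; the article gives no figure. The unrecorded share of the day is then 8/24 = 33% to 10/24 = 42%. The conclusion does not depend on this range.

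**Step 4: which version supports every listed outcome?** Waking activity can be extracted from a 24 h record. Sleep cannot be recovered from a waking-only record. So 24 h/day serves all the accelerometer outcomes in Table 1, and waking-hours wear serves only activity.

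**Step 5: what is untouched?** The metabolic indices come from blood tests and blood pressure. The PSQI (sleep) and the IPAQ-A (activity) are questionnaires. None of these depends on how long the device is worn.

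**The case against.** The strongest reply is that the plan does specify night wear for sleep. Three of the four wear statements say 24 h/day, and the waking-hours phrase sits in a paragraph about activity. On that view, sleep data are lost only if staff apply that sentence and overlook the explicit sleep instruction. This stands in part. The loss is conditional and is not a fixed property of the plan. It does not remove the contradiction, because Table 1 gives 24 h/day for activity as well.

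It is also fair to say that the consequence is confined to secondary outcomes, and that sleep and activity each keep a questionnaire measure.

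A reader might infer more than the article supports:

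- **That activity and sleep share one recording week.** This is plausible but not stated. Step 2 shows that the activity conflict does not need it.
- **That mixed wear biases sedentary time and sleep in opposite directions.** Sedentary time is not a listed outcome. How non-wear is told apart from sleep is a scoring matter that an article commonly leaves to fuller documents.
- **That the arms wear the device unequally.** The Control group section says controls receive and wear the same accelerometers and gives no schedule. Silence on the schedule does not show a difference.
- **That daily team reporting conflicts with the seven-day measurement.** Intervention families are to "report the daily information (include: data recorded by Actigraph wGT3X-BT", and the article describes the device as one of the means of delivering the package. A device can serve both uses, and self-monitoring is then part of the intervention being tested. Removing the report, or imposing daily wear on controls, would change the intervention or the comparator and not merely the wording.

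**Conclusion.** The concern holds as an internal contradiction in the wear instruction, with a conditional consequence.

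- **Certain from the text:** physical activity has two incompatible wear rules, and the only instruction worded for children is the one that cannot support the objective sleep outcomes.
- **Conditional:** if that instruction is issued, all four objective sleep parameters are lost and sleep health rests on the PSQI alone. If practice is mixed, accelerometer wear time is not comparable between children.
- **Not affected:** the primary metabolic outcomes and the questionnaire measures.

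The conclusion assumes only that a device worn in waking hours is off during sleep. The article does not show which instruction was given in practice, so it cannot be said that sleep data will be missing. The point should be corrected because sleep health belongs to the stated second aim and the correction is nearly free, but it does not threaten the main result.

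**What to change.** Change the wear sentence in the activity paragraph to seven consecutive days at 24 h/day on the non-dominant wrist, removed only for water-based activities. That matches both accelerometer rows of Table 1 and the sleep paragraph. State that the same instruction is given to both arms at each assessment, and that waking activity is derived from the 24 h record.

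The cost is one sentence and the matching participant instructions. The device and the number of days do not change. The one downside is that some children may tolerate night wear less well, which could reduce the number of usable nights. No change is needed to the daily team report, the intervention package or the control condition.
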